### Procedure

The study will be conducted in the following 3 phases:

T0: recruitment and baseline data collectionT1: intervention and secondary outcome data collectionT2: follow-up at 6 months (primary outcome and secondary outcome data collection)

At T0, an invitation letter, a consent form, and the baseline questionnaire (questionnaire 1) that allows us to verify the eligibility criteria and calculate the CRC risk score will be sent to the potential participants by the Vaud CRC screening program. The ID codes for the participants will be generated using the IDGenerator, a software tool that was specifically developed for epidemiological and clinical trials [21]. The risk score will be calculated for all eligible individuals who return the signed consent form; subsequently, they will be randomized to either the intervention group or the control group. All individuals who do not respond within 1 month after the first mailing will receive a reminder.

At T1, enrolled participants will receive the intervention or a usual care brochure (in accordance with their group allocation), questionnaire 2, and an information sheet that they can provide to their general practitioner and pharmacist regarding their participation in the study. The participants who do not respond to questionnaire 2 within 2 weeks will be sent a reminder. Qualitative interviews will be conducted with willing participants at this time.

Six months after the intervention, at T2, participants will be contacted again to measure their screening behavior using questionnaire 3. Their responses will be accepted up to 8 months after the intervention. In case of nonresponse within 2 weeks, they will receive a reminder.

All 3 questionnaires, information materials for the participants, and the consent form will be available in both paper and electronic formats. Participants can choose the format that is more convenient to them. All data will be entered into the REDCap (Research Electronic Data Capture; Vanderbilt University) platform [22,23].

Refer to Table 1 and Figures 1 and 2 for procedure details.

**Table 1 table1:** Schedule of enrollment, intervention, and assessments.

		Study period			
		Enrollment	Allocation	After the allocation	
		T0^a^	0	T1^b^	T2^c^

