**Assessments**					
	Baseline variables: eligibility, risk factors for CRC, previous screening recommendations from a GP^e^, knowledge about screening for CRC, demographics, and contact information	✓			
	Main outcome variables: FIT^f^ uptake, colonoscopy uptake or appointment for colonoscopy				✓
	Secondary outcome variables				
	Intention for screening	✓		✓	✓
	Results of the undertaken screening test				✓
	Self-efficacy for screening tests			✓	
	Emotional reaction to the received risk score			✓	
	Perceived barriers to screening			✓	✓
	Perceived benefits from screening			✓	
	Perceived susceptibility for CRC			✓	
	Quality of the brochure and acceptability of the screening recommendations			✓	

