### Outcome Measures

The primary outcome measure is the self-reported appropriate screening uptake 6 to 8 months after the intervention (T2), measured using a short self-administered questionnaire. As waiting times can be long for screening colonoscopies [18], participants who have fixed a colonoscopy appointment will be counted as having undergone a colonoscopy. For the secondary outcome measures, refer to Textbox 2, and for the additional measures, refer to Textbox 3.

Refer to Multimedia Appendix 2 for the English version of the questionnaires and Multimedia Appendix 3 for the French version.

Secondary outcome measures.Self-reported overall screening participation measured at T2 (follow-up at 6 months): on the basis of the participants’ responses at T2, we will calculate the proportion of those who have completed any colorectal cancer (CRC) screening test (fecal immunochemical test or colonoscopy)Participation in the study at 6 weeks after the invitation letter was sent out: we will calculate the number of fully completed electronic or paper questionnairesEligibility for the Vaud CRC screening program at 6 weeks after the invitation letter was sent out: we will calculate the proportion of those who are eligible for the Vaud screening program (eg, not up to date with screening, not in colonoscopy surveillance, and no personal CRC history)Self-reported anxiety related to the intervention and control materials measured at T1 (intervention) using 6 items inspired by the State-Trait Anxiety Inventory [24]Linkage to the Vaud CRC screening program assessed at 3 to 6 months after the primary outcome measurement: we will calculate the proportion of study participants who consent and whose screening status is obtained from the Vaud CRC screening programLinkage to the Vaud cancer registry up to 10 years after the primary outcome measurement: we will calculate the proportion of study participants who consent and whose cancer status is obtained from the Vaud cancer registry (a long time frame has been chosen in view of the delay in updating the cancer registry records and interest in cancer outcomes several years after the primary outcome measurement)

Additional measures.

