### Randomization and Blinding

Randomization will be carried out automatically via the REDCap randomization module programmed by the trial statistician. We will apply a stratified block randomization strategy with a block factor of 8 to prevent a possible imbalance between the control and intervention groups, especially among participants at high risk. The participants will be blinded to the group allocation. They will be told that the study compares 2 slightly different brochures about CRC screening options; however, the nature of the intervention will not be disclosed. The investigators will not be blinded, but, owing to the automatic randomization, they will not be able to influence the participants’ group allocation. The analysis of the main study outcome will be performed by the trial statistician who will be blinded to the participants’ allocation.

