#### Quantitative Data Analysis Plan

The study data will be summarized across all participants by group and by risk level. Continuous and count variables will be summarized as mean (SD) or median (IQR) and categorical variables as number (percentage). To test randomization quality, differences on the baseline variables will be examined using a 2-tailed *t* test for continuous variables and a 2-tailed chi-squared test for categorical variables.

Self-reported appropriate screening uptake will be analyzed using a 2-tailed chi-squared test and controlled for the CRC risk level. Data analysis will be performed using R statistical software (R Foundation for Statistical Computing) [31] and Stata 16 software (StataCorp LLC) [32].

For the primary outcome, participants lost to follow-up will be considered as having refused to participate in screening. If there seems to be differential loss to follow-up between the intervention and control groups, we may perform multiple imputation based on baseline factors as an exploratory analysis. For other secondary outcomes, data will be considered missing completely at random.

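### The exploratory imputation for differential loss is tied to baseline factors; adding the T1 measures and imputing by arm would cover loss that runs through the reaction to the brochure

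*Protocol article*

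**What the plan says.** The Quantitative Data Analysis Plan fixes the primary rule: "For the primary outcome, participants lost to follow-up will be considered as having refused to participate in screening". It states one alternative, under a condition: "If there seems to be differential loss to follow-up between the intervention and control groups", then "we may perform multiple imputation based on baseline factors as an exploratory analysis". It names no variable measured after randomisation for that model, and it does not say whether arm enters it.

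Other sections bear on the choice:

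- **Table 1.** "Intention for screening" is ticked at T0, T1 and T2. Self-efficacy and perceived susceptibility, benefits and barriers are ticked at T1, as is "Emotional reaction to the received risk score".
- **Textbox 2 (secondary outcomes).** "Self-reported anxiety related to the intervention and control materials measured at T1" is listed, so this measure covers both arms.
- **Textbox 3 (additional measures).** Intention and test preference are also collected at T0.
- **Intervention and Usual Care Materials, and Table 2.** The intervention brochure varies with risk level. All controls receive one brochure, without a score.
- **Theoretical Framework.** Screening behaviour is expected to depend largely on perceived susceptibility and on beliefs about self-efficacy and the efficacy of screening.
- **Procedure.** T1 has its own non-response: "The participants who do not respond to questionnaire 2 within 2 weeks will be sent a reminder".

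**The concern.** The imputation is reserved for loss that differs between arms. According to the Procedure section, everyone follows the same path through T0, and randomisation comes after it. The first planned difference between the arms is the brochure. Apart from chance, differential loss must therefore arise from the response to it, either alone or in combination with baseline characteristics.

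The article's own theory says that the brochure should shift beliefs measured at T1, and that these beliefs drive uptake. If they also influence who returns questionnaire 3, they link loss to the outcome. A model limited to T0 variables cannot remove that link, although for people who returned questionnaire 2 but not questionnaire 3 the relevant data are on file.

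At stake is how this check is read. It is the only stated alternative to counting lost participants as unscreened, and in the situation it was written for it could carry a selection bias of its own.

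**Working it through.** **The plan's own figures.** The sample size section compares 46% with 56% at two-sided α = 5% and 80% power. With pooled variance under the null:

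n = [1.960·√(2·0.51·0.49) + 0.842·√(0.46·0.54 + 0.56·0.44)]² / 0.10² = 391.1, rounded up to 392 per arm, as stated.

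The point does not depend on this figure; it only anchors the illustration. Table 3 gives risk strata of 60/30/10%. Appropriate screening is about 35/70/35% in controls and 50/70/50% with the intervention:

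- control: 0.6·0.35 + 0.3·0.70 + 0.1·0.35 = 45.5% (Table 3: 179/392 = 45.7%)
- intervention: 0.6·0.50 + 0.3·0.70 + 0.1·0.50 = 56.0% (Table 3: 220/392 = 56.1%)
- true difference: 10.5 points

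The loss and reaction rates below are assumptions. The article gives only about 10% attrition overall. Imputation is taken within arm, in large samples.

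**1. Loss depends on baseline only, alike in both arms.** With loss of 12/6/10% by low/moderate/high risk, each arm loses 0.6·12 + 0.3·6 + 0.1·10 = 10.0%. There is no differential loss, so the imputation would not be triggered.

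**2. Loss depends on arm by risk level.** Controls lose 8%. The intervention arm loses 20/5/10%, overall 0.6·20 + 0.3·5 + 0.1·10 = 14.5%. The complete-case intervention rate is (0.6·0.80·0.50 + 0.3·0.95·0.70 + 0.1·0.90·0.50)/0.855 = 0.4845/0.855 = 56.7%, a difference of 11.2 points. Imputing within arm and risk level restores 10.5. Baseline factors suffice.

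**3. Loss depends on arm alone (8% v 15%).** Within each arm the observed rate equals the true rate, so the estimate is 10.5. Baseline factors suffice.

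**4. Loss runs through the T1 reaction.** An adverse reaction occurs in 20% of controls and 40% of the intervention arm. Loss is 30% with it and 4% without, and the reaction lowers uptake by 20 points.

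- Loss: control 0.2·30 + 0.8·4 = 9.2%; intervention 0.4·30 + 0.6·4 = 14.4%.
- Reactors among those observed: control 0.14/0.908 = 15.4%; intervention 0.28/0.856 = 32.7%.
- Upward shift in the observed rate: control 0.20·(20 − 15.42) = 0.92 points; intervention 0.20·(40 − 32.71) = 1.46 points.
- Estimate: 10.5 + (1.46 − 0.92) = 11.0 points.

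Because loss here is unrelated to risk level, imputing on risk level leaves the complete-case answer unchanged. Imputing on risk level and reaction within arm restores 10.5. A simulation of 4,000,000 people gave 11.1, 11.1 and 10.5 for complete cases, baseline-only imputation and baseline plus T1.

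**Range for case 4.** The reaction's effect on uptake runs from 10 to 30 points and loss among reactors from 20 to 40%.

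- Smallest: 0.10·[(40 − 35.71) − (20 − 17.24)] = 0.15 points.
- Largest: 0.30·[(40 − 29.41) − (20 − 13.51)] = 1.23 points.

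The simulation, read from rounded output, gave 0.2 to 1.3. The bias is upward throughout this range. Its direction follows from the assumption that the reaction is commoner in the intervention arm and lowers uptake.

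**Scale.** In the simulated scenarios with differential loss, the primary rule (lost = unscreened) gave 5.6 to 8.3 points. It moves the estimate further than the choice of imputation variables does.

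**The case against.** The strongest objection concerns the criterion. Imputation does not need predictors that explain why loss rates differ. It needs loss to be independent of the outcome given arm and the predictors. Cases 2 and 3 meet that condition with baseline variables alone, and case 2 is realistic because the intervention brochure differs by risk level. This stands. A reader might infer that baseline factors, being balanced, can never account for differential loss. That is too strong: balance rules out only effects common to both arms. Baseline intention and test preference may also carry part of the reaction's influence.

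A reader might also infer that the model omits arm. The sentence is silent on this. It is an article's short description of covariates and says nothing about pooling the arms. That is a reason to name arm, not evidence of an error.

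The remedy has limits too. People put off by the brochure may return neither questionnaire 2 nor questionnaire 3, so T1 data may be missing where they matter most. The item on emotional reaction to the score has no direct counterpart in controls.

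Finally, imputation predictors are usually settled in the SAP, which is not shown and may list more. The article does name a predictor set, though, so what is questioned is a stated choice and not an absent detail.

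**Conclusion.** The point holds as a conditional one. Baseline-only imputation is adequate if loss is unrelated to the outcome given arm and baseline. If loss runs through a reaction to the brochure that also predicts uptake, it leaves the selection in place, with an overstatement of about 0.2 to 1.2 points on a true 10.5 (0.2 to 1.3 in simulation). That size rests on the assumed reaction rates, loss rates and effects on uptake, and on T1 data being complete; the documents allow none of these to be checked by arm.

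The stakes are low. The analysis is optional and exploratory, and it does not replace the primary rule. The documents do not support reading this as a flaw in the primary result. It is a cheap improvement.

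**What to change.** In the Quantitative Data Analysis Plan, replace the phrase that ties the imputation to baseline factors with a statement that:

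- the T2 outcome is imputed separately by arm, or with arm interactions;
- the model includes risk level, baseline intention and baseline test preference;
- T1 measures available in both arms enter as auxiliary variables: intention, anxiety about the materials, self-efficacy, and perceived susceptibility, barriers and benefits;
- missing T1 values are imputed in the same model.

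The emotional-reaction item should not be relied on, since controls receive no score.

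The cost is one sentence and a somewhat larger model. All the variables were scheduled for collection, so no new data are needed. The drawback is that T1 values will be missing for some people lost at T2, so the correction may be partial; reporting how many of those lost had returned questionnaire 2 would show how far it reaches. Because the article reports data collection as complete, the change should be dated and, if made after outcomes by arm were seen, labelled post hoc.

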However, the impact of personalized screening on the screening test choice remains unclear. A meta-analysis has shown that personalized risk communication alone does not improve the overall uptake of screening tests [17]. Indeed, communicating personalized risk without giving clear screening recommendations may have no influence on screening behavior or even decrease it. This is in accordance with the view that providing people with threatening information only can decrease desired health behaviors if people cannot cope with the threatening information. However, the studies included in the meta-analysis did not address the choice between the FIT and colonoscopy and contain some important methodological discrepancies.

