### Participants

We plan to send out 4300 invitations to recruit 880 eligible participants (Figure 1). Refer to Textbox 1 for the inclusion and exclusion criteria.

Our exclusion criteria allow for the exclusion of individuals at very high risk of CRC (Textbox 1), enabling us to avoid inviting to the study those who are ineligible for the Vaud screening program. Individuals at very high risk are identified using a questionnaire to screen for current symptoms of possible CRC, personal history of CRC or polyp requiring surveillance, inflammatory bowel disease, and genetic syndromes.

Participants can stop their participation at any time without providing any justification. They will be informed that screening uptake is not mandatory and that withdrawal of consent will not affect their subsequent participation in the Vaud screening program.

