To increase the participants’ perceived response efficacy, our intervention materials emphasize information about the advantages of the recommended test for their risk level. However, the intervention brochure does present an alternative to screening, thus offering a choice to the participants. Moreover, all intervention group participants will receive an information sheet suggesting that they discuss their risk level with their general practitioner.

The intervention brochure will contain recommendations corresponding to the risk level of each participant only. We expect that this will facilitate the understanding of the provided information, minimize reading effort, and enhance adherence to our recommendations. Refer to Table 2 for more information about the content of each brochure category. For the sake of brevity, the intervention brochures will not communicate the side effects or sensitivity of the tests. Both the FIT and colonoscopy are screening tests commonly used in Switzerland and are considered safe and efficient to significantly reduce CRC mortality if undergone within the recommended period (the FIT every 2 years and colonoscopy every 10 years).

The control brochure represents the usual brochure that the Vaud screening program provides to individuals eligible for CRC screening. This brochure recommends screening to all individuals beginning at age 50 years and presents both the FIT and colonoscopy as equal options. This brochure does not include either a personalized risk score or specific screening recommendations. This suggests that, in the control group, the screening tests will be chosen according to the participants’ preferences or after discussion with their primary care physician rather than in accordance with their risk level.

**Table 2 table2:** The different kinds of information presented in the printed materials.

Information presented in the brochure	Intervention brochure				Control brochure
	High risk	Low risk	Moderate risk		
Information about CRC^a^	Yes	Yes	Yes	Yes	
Information about screening benefits	Yes	Yes	Yes	Yes	
Explanation concerning risk levels and how they can be calculated	Yes	Yes	Yes	No	
Personalized risk score	Yes	Yes	Yes	No	
Screening recommendations	Personalized: colonoscopy recommended; the FIT^b^ as an alternative	Personalized: the FIT is recommended; colonoscopy as an alternative	Personalized: the FIT and colonoscopy are equal options	General: the FIT and colonoscopy are equal options	

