## Results

### Overview

As of September 2022, a total of 515 participants had been enrolled in the trial and sent intervention or control materials. Six months later, 98.8% (509/515) of the enrolled individuals were sent the follow-up questionnaire. Data collection was completed on July 24, 2023 (6-8 months after the intervention).

We expect that the proportion of participants who complete the screening test appropriate to their risk level will be higher in the intervention group than in the control group, except for the individuals at moderate risk. The proportion of participants at moderate risk in the intervention group is expected to be the same as that of the participants in the control group in screening test choice because both tests are suggested as equal options.

We do not expect any difference in anxiety between the intervention and control groups. A Cochrane review of interventions similar to ours has shown that there was a nonsignificant trend toward decreased anxiety with risk information (standard mean difference in anxiety 0.13, 95% CI −0.29 to 0.03) [17].

Our intervention does not aim to enhance overall screening uptake; therefore, we do not expect any difference between the groups.

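### Missing completely at random is an unjustified assumption for T1 anxiety, because questionnaire 2 is returned or not after only one arm has seen a personal risk score

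*Protocol article*

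**What the plan says.** The missing-data paragraph of the Quantitative Data Analysis Plan has three parts. For the primary outcome, people lost to follow-up count as not screened. If loss appears to differ by arm, multiple imputation from baseline factors may be done as an exploratory step; this follows on from the primary-outcome rule. The last sentence covers the rest: "For other secondary outcomes, data will be considered missing completely at random".

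Anxiety falls under that last sentence. Outcome Measures (Textbox 2) lists it as "Self-reported anxiety related to the intervention and control materials measured at T1 (intervention) using 6 items inspired by the State-Trait Anxiety Inventory". The Procedure section describes how it is collected: "At T1, enrolled participants will receive the intervention or a usual care brochure (in accordance with their group allocation), questionnaire 2". The stated protection against non-return is one reminder: "The participants who do not respond to questionnaire 2 within 2 weeks will be sent a reminder".

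The arms differ in what they read before answering. Of the control brochure the article says: "This brochure does not include either a personalized risk score or specific screening recommendations". The Results overview gives the expected finding: "We do not expect any difference in anxiety between the intervention and control groups". Under Data Collection, anxiety also appears among the adverse-event information.

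**The concern.** Missing completely at random requires non-return to be unrelated to arm, risk level and the anxiety score itself. Here every non-return of questionnaire 2 happens after randomization and after a stimulus that differs between the arms and, within the intervention arm, between risk levels. The article gives no reason why return should be unrelated to that stimulus. Its own paragraph allows that loss could differ by arm, but the imputation offered there is optional, exploratory and tied to the primary outcome. Nothing stated protects the anxiety comparison.

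The sentence does not name the resulting analysis. The usual consequence is a comparison of those who returned the questionnaire, and that is what is examined below. At stake is how far the anxiety result can be trusted. The expected result is a null, and a null in responders alone cannot be told apart from a real increase that non-return has hidden.

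**Working it through.** **Plan's own figure.** The article states no SD, effect size or power for anxiety. Its one sample-size figure concerns the primary outcome and reproduces. With 46% v 56%, two-sided 5% and 80% power, n = [1.96·√(2·0.51·0.49) + 0.842·√(0.46·0.54 + 0.56·0.44)]² / 0.10² ≈ 391.1, so 392 per arm. Dividing by 0.9 gives 436, against the stated 440. This neither supports nor weakens the point on anxiety.

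**Inputs.**
- From the article: 440 per arm planned with about 10% attrition, so 440 × 0.9 = 396 responders; high risk expected in 10%.
- Not in the article, so assumed: non-return r_int of 10% to 20% in the intervention arm and r_ctl at half that in control; non-responders d = 0.3 to 0.5 SD more anxious than responders.

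**Formula.** In each arm, full mean = responder mean + r·d. Hence

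bias of the responder difference (intervention minus control) = −(r_int·d_int − r_ctl·d_ctl).

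If d = 0 in both arms there is no bias, however unequal the return rates. The harm needs a link between return and anxiety.

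**Results.**

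| Scenario | Arithmetic | Bias (SD) |
|---|---|---|
| Same d in both arms, low end | 0.3 × (0.10 − 0.05) | −0.015 |
| Same d in both arms, high end | 0.5 × (0.20 − 0.10) | −0.05 |
| Informative in intervention arm only, low end | 0.3 × 0.10 | −0.03 |
| Informative in intervention arm only, high end | 0.5 × 0.20 | −0.10 |

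If non-responders are the less anxious ones, d is negative and every sign reverses.

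**High-risk stratum only.** Let high-risk people (10%) be D SD more anxious, with non-return h, against 10% non-return in everyone else. The true contribution to the arm mean is 0.1·D. The responders show 0.1(1−h)D / [0.1(1−h) + 0.9·0.9].
- h = 20%, D = 0.5: 0.04/0.89 = 0.045 against 0.05, a bias of −0.005.
- h = 50%, D = 1: 0.05/0.86 = 0.058 against 0.10, a bias of −0.042.

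**Effect on the conclusion.** With 396 per arm the standard error is √(2/396) = 0.071 SD. A true increase of 0.20 SD has 80% power. A bias of −0.05 leaves an apparent 0.15 and 56% power; a bias of −0.10 leaves 0.10 and 29%. These use the planned size. The article reports 515 enrolled as of September 2022. If that were final, 515/2 less 10% is about 232 per arm, the standard error is 0.093, and power for 0.20 SD is 58% before any bias.

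**Direction depends on the truth.** Under a bias of −0.05 to −0.10:
- a true +0.20 becomes +0.15 to +0.10, which is masking;
- a true zero becomes −0.05 to −0.10, a spurious decrease;
- a true −0.13 becomes −0.18 to −0.23, further from no difference. The value −0.13 is the midpoint of the cited interval, (−0.29 + 0.03)/2; the article prints the estimate as 0.13.

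**The case against.** The strongest reply is that nothing in the article shows distress stopping anyone from returning questionnaire 2. That is correct. A reader might infer it from "Participants can stop their participation at any time without providing any justification", but withdrawal appears rare: 509 of 515 were still sent the six-month questionnaire, so at most 6 (1.2%) had left by then. That figure counts people mailed at T2, however, and says nothing about how many returned questionnaire 2.

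A reader might also infer that the rule tilts the result towards the expected null. The article does not support this. It holds only if the more anxious intervention participants return less and the intervention truly raises anxiety. About 60% are expected to be low risk; if reassured people are the ones who do not reply, the bias reverses.

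Two apparent contradictions also fall away. The Background remark that "providing people with threatening information only can decrease desired health behaviors if people cannot cope with the threatening information" concerns health behaviours under risk information without recommendations, and this intervention supplies recommendations. Counting lost participants as unscreened is a convention for a binary uptake outcome with no counterpart for a six-item scale, so having different rules is not inconsistent.

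On size, the main range of 0.015 to 0.05 SD is below one standard error. Excess non-return of 5 to 10 percentage points across the arm could not plausibly come from the high-risk stratum alone, which would need 50 to 100 extra points there.

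Finally, sensitivity analyses are often left to an analysis plan that is not shown. This does not remove the point: the article fixes the assumption itself, and uncertainty about direction and size is a reason to test it.

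**Conclusion.** The point holds in limited form. Missing completely at random is stated, applies to T1 anxiety, is not justified, and is hard to defend when non-return follows an arm-specific message. A responder-only comparison could be biased either way, and one possible result is that a real increase in anxiety goes unseen. Neither the cause of non-return nor the sign of the bias is established.

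The size is unknown without questionnaire 2 return rates. On the assumptions shown it is 0.015 to 0.05 SD in absolute value, up to 0.10 SD if non-return is informative in the intervention arm only, and 0.005 to 0.04 SD if confined to the high-risk stratum. The lower values would matter little; the upper ones would seriously weaken the ability to detect an increase of 0.20 SD. This is one secondary outcome of a pilot trial and does not affect the primary analysis. The change is worth making because it is cheap.

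**What to change.** - **Assumption.** For the questionnaire 2 outcomes, replace missing completely at random with missing at random given arm, risk level and the T0 variables already collected (such as age, sex, screening intention, test preference, previous general-practitioner recommendation and knowledge). Use a model adjusted for these or multiple imputation by arm.
- **Reporting.** Give questionnaire 2 non-return by arm and risk level.
- **Sensitivity analysis for anxiety.** Shift the imputed values of intervention-arm non-responders over a range in both directions, for example ±0.3 and ±0.5 SD, and state whether the conclusion on anxiety holds. At 10% to 20% non-return this moves the estimate by 0.3 × 0.10 = 0.03 to 0.5 × 0.20 = 0.10 SD either way.

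The third item carries most of the weight. Anxiety is not among the T0 measures, so conditioning on baseline cannot recover non-return driven by a reaction to the score. It can deal with non-return that depends on risk level. The delta values are illustrative and should be fixed before anxiety is compared by arm.

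Cost: a few sentences, some programming and a possibly wider interval. No new contact with participants is needed, which matters because data collection is complete.
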